### Randomization:

Participants (including those in the pilot study) will be randomized to the two treatment arms using the method of permuted blocks. Randomization sequences will be generated by a statistician, and will be uploaded into the REDCap randomization module. Randomization will be stratified by study site and by risk of neuromotor delay (mild vs. moderate/severe). Siblings in multiple births will be assigned to the same group, and outcomes assessed only for the infant with the most severe risk. In order to ensure unbiased evaluations, assessments of motor function and other outcomes will be performed by different study team members than those administering treatment, and although this is not a blinded study, therapists conducting study evaluations will be blinded to treatment arm assignment whenever possible.

### Data analysis:

The primary analysis to compare 12-month Bayley-4 Motor scores between treatment arms, will be performed using a two-sample two-sided t-test assuming equal variance. Because the Bayley-4 scores are standardized, we expect them to follow the normal distribution. If the normality assumption is not satisfied, the Wilcoxon ranksum test will be used instead. In addition, a covariate adjusted estimate will be obtained using a linear regression model adjusted for known baseline prognostic factors, e.g. risk of neuromotor delay, gestational age at birth, and sex.

Baseline characteristics, study outcomes and treatment compliance rates will be summarized by treatment arm using basic descriptive statistics, e.g. mean, SD, median and inter-quartile range (IQR) for continuous variables, and frequencies and proportions for categorical variables.

To address questions posed in Aims 2 and 3 regarding early differences in outcomes, outcome measures will be summarized at each time point by group, and linear mixed effects models with repeated measures will be used to compare score changes over time between arms. In these models, the outcome measure, e.g., sensor data, PedsQL, GMA and others, will be the dependent variable, and predictors will include treatment arm and assessment time point as fixed effects and subject as the random effect. Within-subject correlation between repeated measurements will be accounted for by using an appropriate variance-covariance structure, e.g. autoregressive order 1 (AR(1)). Interactions between time and treatment may also be included as a fixed effect. Additional baseline prognostic covariates may also be included in the model as fixed effects to obtain covariate-adjusted estimates that may be more efficient. Differences between arms at early time points will be estimated based on the fitted model by constructing appropriate contrasts, and compared using post hoc tests. Separate models will be fitted for each outcome measure. Of note, this approach appropriately deals with missing data by including all evaluable observations across time points, rather than performing a complete case analysis. Analyses will be conducted using PROC MIXED in SAS statistical software. P-values will not be adjusted across these outcome measures because these are pre-specified analyses for outcome measures that address different aspects of the intervention.

In addition, the dose-response relationship between the number of home visits during the 12-month period (dose) and 12-month outcomes (response) will be examined among patients randomized to the treatment arm. Data will be graphically examined using scatter plots with an overlaid lowess smoother, and linear regression models will be fitted with the 12-month outcome measure as the dependent variable, and number of visits as the predictor. Nonlinear terms may be included for the number of visits (x-variable) to model the potentially nonlinear association. These models may also be adjusted for important baseline prognostic covariates as for the primary outcome measure.

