- Subdural, subarachnoid, or subgaleal hemorrhage with otherwise normal MRI and no seizures
- Mild abnormalities on cranial ultrasound or MRI (including, but not limited to, non-cystic periventricular leukomalacia (PVL) or mild white matter injury)
- BW<1500 grams with grade 0, 1 or 2 intraventricular hemorrhage (IVH)
- No BPD or Jensen Grade 1 nasal cannula (NC) ≤ 2 liters per minute LPM) at 36 weeks

*Moderate-Severe risk:*

- Clinical HIE diagnosis or meningitis with abnormal MRI OR seizures
- Grade III/IV hemorrhage
- Cystic PVL
- Ventriculoperitoneal (VP) shunt
- Stroke
- Cramped synchronous movements
- BPD (respiratory support > 2 LPM NC at 36 weeks)
- Brain developmental abnormalities (hydrocephalus, microcephaly, cortical dysgenesis)
- Other surgical or medical condition likely to increase risk of neuromotor delay based on clinical judgement, at the discretion of the PI

*Intervention:*

*NICU:* The NICU intervention sessions (approximately 40 minutes to one hour) will be provided 1-2 times per week, based on caregiver needs and infant tolerance. Intervention sessions will be scheduled after completion of baseline assessment until discharge from the NICU. Intervention therapists may work with project coordinators, allied health professionals, and caregivers for appropriate timing of the intervention sessions. An attempt to reschedule any missed sessions will be made. At the beginning of each session, intervention therapists will review any changes in infant status/state with caregivers and/or allied health professionals. They will work collaboratively with caregivers to identify the infant’s current state of arousal, monitor for significant and consistent stress signals during the session, and modify activity selection based on infant tolerance. Staff will record session outcomes and complete appropriate forms in REDCap. For infants that may require additional support during intervention sessions (infants who require respiratory support >2 LPM nasal cannula and others based on bedside nurse recommendation) a research nurse will attend the intervention or assessment to monitor the infant.

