*Assessments*: All enrolled participants will follow the same assessment timeline (Table 1). Assessments will be completed at study enrollment and thereafter at monthly intervals up to 3 months corrected age, then at 3-months corrected age, 6-months corrected age, 9-months corrected age, 12-months corrected age, 18-months corrected age (optional), and 24-months corrected age (optional). The number of assessments prior to 3 months corrected age will vary by preterm status and age of enrollment. If infants are unable to complete a scheduled assessment session, efforts will be made to re-schedule. Flexibility in location (home vs. in-clinic) of assessment will be made available as necessary. Families will be screened for COVID-19 prior to each assessment session. If any member of the family is unwell or there is a known exposure to COVID-19, the session will be rescheduled or conducted via telemedicine where possible, following hospital guidelines. Assessments may be completed over several days depending on caregiver and infant needs. If infants are unable to complete a testing session, their participation in the study will not be impacted, however, the study team will appropriately document this issue. Assessment therapists will self-screen for COVID-19 symptoms or exposures before starting work each day, and will follow all clinic COVID-19 protocols. **Assessments in** **bold** in Table 1 are part of standard clinical care in the Early Childhood Clinic and would be done regardless of study participation (i.e., these are not study-specific procedures).

*Primary Outcome Measure:* Bayley-4 motor score at 12-months corrected age

*Secondary Assessments and/or Outcome Measures:* Sensors, PedsQL, Bayley-4 (cognitive)

*Exploratory Assessments and/or Outcome Measures:* GMA, NSMDA, TIMP, HINE, AIMs, PEDI-CAT, WIDEA-FS

*Assessments*:

| **Enrollment: Pre-term or Term Age** | **Monthly up to 3 months CA** | **3-months CA** | **6-months CA** | **9-months CA** | **12-months CA** | **18-months CA** | **24-months CA** |
| --- | --- | --- | --- | --- | --- | --- | --- |
|  |  |  | **Bayley-4^§^** |  | **Bayley-4^§^*** | **Bayley-4^§^** | Bayley-4**^§^** |
| **GMA**** | **GMA** | **GMA** |  |  |  |  |  |
|  |  |  | AIMS | AIMS | AIMS |  |  |
| Sensors | Sensors | Sensors | Sensors | Sensors | Sensors | Sensors | Sensors |
|  |  | NSMDA |  | NSMDA | NSMDA | NSMDA | NSMDA |
| TIMP | TIMP | TIMP |  |  |  |  |  |
|  |  | **HINE** | **HINE** | HINE | **HINE** |  |  |

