- **The Hammersmith Infant Neurological Exam (HINE)**: The HINE comprises 26-items, spanning five domains: cranial nerve function, posture, quality and quantity of movements, muscle tone, and reflexes and reactions. Each item is given a score between 0 and 3 based on a rubric, with a maximum possible summed score across all items of 78. Infants will be video recorded. This is a routine test at all study ages in the Early Childhood Clinic.
- **Neurological, Sensory, Motor, Developmental Assessment (NSMDA)**: The NSMDA measures neurodevelopment between 1-month and 6-years of age. It is composed of five domains: neurological, postural, sensory, fine motor, and gross motor. Each domain is provided a total functional grade of normal, minimal deviation, mild deviation, moderate deviation, severe deviation, or profound deviation. This assessment demonstrates predictive validity for long-term motor development. This test is often but not always part of the Early Childhood Clinic assessment.
- **Alberta Infant Motor Scale (AIMS):** The AIMS is a norm referenced, standardized, gross motor assessment. Infants are observed in four positions: prone, sitting, supine, and standing. For each subscale, items are scored as “observed” or “not observed”. The items in the observed range create a motor window. A total raw score is calculated and a percentile rank is given based on a sample of 2202 infants from Alberta, Canada. The AIMS has been reported to have reliability, concurrent and predictive validity. The duration of this assessment is approximately 10-20 minutes. Infants will be video recorded. This is not a typical Early Childhood Clinic test.
- **Test of Infant Motor Performance (TIMP):** The TIMP is a 42-item assessment of postural and selective motor control of functional performance in infants between 34 weeks and 4 months corrected age. Items are either observed (13) or elicited (29). Observed items (1-13) are scored yes (1 point) or no (0 points); elicited items (14-42) are scored from 0-3, 0-4, 0-5, or 0-6). Item scores are summed, and infants receive an age standard score, based on performance, of average, low average, below average, or far below average. The maximum possible score is 142. This is not typically done in the Early Childhood Clinic.

*Sensor Data*:

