# Data Management and Confidentiality

***Data Analysis Plan***

### Power Analysis:

The motor subscale score of the Bayley-4 at 12-months corrected age is the primary outcome measure. It is a standardized score with a range of 45-155, a mean of 100, and a standard deviation (SD)=15. For this study, we will consider a significant effect of the intervention to be a Bayley motor score that is 8 points (~0.5 SD) higher in the intervention group than in the control group at 12-months corrected age. Assuming similar variability in this clinical trial with SD=15, a sample size of n=77 subjects per arm will provide 90.1% power with two-sided α=0.05 significance level to detect an 8-point difference in Bayley-4 motor scores at 12 months based on a two-sample equal-variance t-test. This would correspond, for example, to an improvement from the average 12-month Bayley-4 Motor score of 87.7 among patients (n = 77) recently assessed in our Early Childhood Clinic to an average score of 95.7. If we conservatively assume larger SD=17.5 due to possibly higher variability in Bayley-4 Motor scores in this high-risk population, we would still have sufficient 79.4% power to detect an 8-point difference between treatment arms. Assuming 30% attrition, up to 220 patients (110 per arm) will be required in order to obtain 154 patients evaluable for primary outcome. Assuming 20% attrition, up to 192 patients (96 per arm) will be required in order to obtain 154 patients evaluable for primary outcome. Power calculations were done using PASS 2020 software.

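### The supplementary adjusted estimate of the 12-month Bayley-4 Motor effect names no measured baseline motor score, although the TIMP is collected at enrolment in both arms

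*Protocol*

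**What the plan says.** In the Protocol's Data analysis section, the 12-month Bayley-4 Motor scores are compared by a two-sided equal-variance t-test, with the Wilcoxon test if normality fails. A linear regression then supplies a further estimate, "adjusted for known baseline prognostic factors, e.g. risk of neuromotor delay, gestational age at birth, and sex". The three covariates are given as examples.

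Table 1 (Procedures Involved) starts the Bayley-4 at 6 months, so the outcome has no enrolment value. The TIMP row reads "TIMP | TIMP | TIMP": enrolment, monthly to 3 months, and 3 months corrected age. Both arms follow this schedule. The TIMP is described as an "assessment of postural and selective motor control of functional performance in infants between 34 weeks and 4 months corrected age" with a maximum score of 142. That age range covers the 34-48 week postmenstrual age (PMA) window for starting the intervention. On order, the NICU paragraph says: "Intervention sessions will be scheduled after completion of baseline assessment until discharge from the NICU".

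The TIMP otherwise appears as an Aim 2 measure and in the list of exploratory measures. Nothing names it as a covariate for the primary outcome, and nothing excludes it.

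**The concern.** When the outcome cannot be measured at entry, the nearest earlier measure of the same ability is the natural covariate. Here that is the enrolment TIMP. The named covariates carry motor status only through a two-level risk class, and each level is broad. The mild class runs from infants merely at risk for HIE to those with mild white matter injury. The moderate-severe class covers stroke, cystic PVL, more severe BPD and a discretionary category. Infants in one class may differ widely in starting motor performance.

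Without a measured baseline, any outcome variance that starting performance explains beyond risk, gestational age and sex stays in the error term. A chance imbalance in starting performance between arms also goes uncorrected in the adjusted estimate. What is at stake is the width of that estimate's confidence interval. The Data analysis section already accepts the principle for its mixed models, where it notes that covariate adjustment may be more efficient.

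**Working it through.** **Inputs.** From Power Analysis: "The motor subscale score of the Bayley-4 at 12-months corrected age is the primary outcome measure". The target difference is "8 points (~0.5 SD) higher in the intervention group than in the control group at 12-months corrected age". There are 77 evaluable infants per arm and a two-sided 0.05 level. The base case is "Assuming similar variability in this clinical trial with SD=15". The cautious case is SD 17.5, where "we would still have sufficient 79.4% power to detect an 8-point difference between treatment arms". Two inputs are not in the documents and are assumed over a range:
- R², the share of outcome variance explained by risk, gestational age and sex;
- r, the partial correlation of the enrolment TIMP with the 12-month score, given those covariates and PMA at test.

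**Step 1: the plan's own power.** SE = SD × √(2/77), with power from the noncentral t on 152 df.
- SD 15: SE = 2.42, power 90.8% (stated 90.1%).
- SD 17.5: SE = 2.82, power 80.5% (stated 79.4%).

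Both reproduce to within about one point.

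**Step 2: the adjusted model with the named covariates.** Residual SD = SD × √(1 − R²). With R² = 0.20:
- SD 15: residual SD 13.42, SE 2.16.
- SD 17.5: residual SD 15.65, SE 2.52.

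If this model carried the test (154 − 5 = 149 residual df), power at SD 17.5 would be 88.3%.

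**Step 3: add the TIMP.** The partial correlation acts on the Step 2 residual SD: new SE = Step 2 SE × √(1 − r²). The information ratio is 1/(1 − r²), so 154 infants are worth 154/(1 − r²) relative to the Step 2 model. The percentage fall in SE does not depend on SD or R².

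| r | Fall in SE | 154 infants worth | SE, SD 15 | SE, SD 17.5 | Power at SD 17.5, only if the adjusted model is primary |
|---|---|---|---|---|---|
| none | – | 154 | 2.16 | 2.52 | 88.3% |
| 0.1 | 0.5% | 156 | 2.15 | 2.51 | 88.6% |
| 0.2 | 2.0% | 160 | 2.12 | 2.47 | 89.5% |
| 0.3 | 4.6% | 169 | 2.06 | 2.41 | 91.0% |
| 0.4 | 8.3% | 183 | 1.98 | 2.31 | 93.0% |
| 0.5 | 13.4% | 205 | 1.87 | 2.18 | 95.3% |

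The SE columns and the power column use R² = 0.20. Power is for a fixed-sample test at two-sided 0.05, as in the protocol's own calculation, and ignores the interim analysis.

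**Step 4: sensitivity to R².** At SD 17.5 with the adjusted model as primary, R² = 0.10 gives 84.4% without the TIMP and 85.8% to 92.9% for r = 0.2 to 0.5. R² = 0.30 gives 92.1%, and 93.0% to 97.3%.

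**Step 5: cost in degrees of freedom.** TIMP, PMA at test and a missing-score indicator take the residual df from 149 to 146. The two-sided 5% critical value moves from 1.9760 to 1.9763, which is negligible.

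**The case against.** Five objections deserve an answer.

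- **The covariate list is illustrative.** A reader might infer that the TIMP has been ruled out. The documents do not support that: the list is open, and the SAP, not at hand, may settle it. This stands as a limit on wording: the TIMP is unnamed, not excluded. But the protocol chose to give examples, none is a measured motor score, and a suitable one is already collected.
- **The primary test is untouched.** A reader might infer that the trial's deciding test is less powerful than it could be, and that naming the TIMP repairs this. It does not. The stated power belongs to the unadjusted t-test, and adding a covariate to a supplementary regression changes that power by nothing. This stands in full.
- **The gain is easily overstated.** Applying r to the full SD of 17.5 gives power rising from 80.5% to 82.0%, 84.0%, 86.8% and 90.2% for r = 0.2 to 0.5, or gains of 1.5, 3.5, 6.3 and 9.7 points. That treats risk, gestational age and sex as explaining nothing. With R² = 0.20 the gains are 1.2, 2.7, 4.7 and 7.0 points, and even those need the adjusted model to be primary. At r = 0.1 the gain is trivial.
- **The score is not shown to be masked or pre-randomisation.** Procedures Involved ties randomisation only to consent. The ordering rule covers NICU sessions, while Consent Process allows consent after discharge. The Randomization section blinds assessors only where possible, and 29 of the 42 TIMP items are examiner-elicited. This stands and calls for a safeguard in the fix.
- **Other enrolment measures exist.** The GMA and sensor data are also taken at enrolment, and the risk class already reflects imaging, BPD severity and cramped synchronous movements. That may make r small. It does not remove the case for a summed motor score that is already scheduled.

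**Conclusion.** The point holds as a missed efficiency gain in the supplementary adjusted estimate. The enrolment TIMP is scored, scheduled in both arms, placed before NICU treatment and suited to the entry ages, yet it is not among the named covariates. Its inclusion would cut the adjusted SE by about 0.5%, 2%, 5%, 8% or 13% for partial correlations of 0.1 to 0.5. Those correlations are assumptions, so the gain may be negligible or worthwhile, and the documents cannot say which.

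The power figures are conditional on two further assumptions: that the sponsor makes the adjusted model primary, and that the named covariates explain 20% of variance.

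A reader might also infer that the effect estimate is biased or the type I error inflated. Neither follows: leaving a baseline covariate out of a randomised comparison of means costs precision only.

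**What to change.** In the Data analysis section, prespecify that the 12-month Bayley-4 Motor regression includes the enrolment TIMP raw score and PMA at that test, alongside risk class, gestational age and sex. Age at test is needed because entry spans 34-48 weeks. The age-standardised score is an alternative, but the protocol describes it in four bands, so the raw score with PMA should keep more information.

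For a missing enrolment TIMP, use the overall mean with a missing-score indicator, so that no infant with a 12-month outcome is dropped from the regression.

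Require that the enrolment TIMP be completed before allocation is revealed to the assessor. Without this, knowledge of the arm could influence the covariate.

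State whether the adjusted model remains supplementary or becomes primary, because only the second choice carries the gain into the trial's main test.

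The cost is a few sentences and two or three degrees of freedom out of about 150. No new test is needed, but sites may have to reorder enrolment steps so that the TIMP comes before the assessor can learn the allocation.

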| PedsQL (once during NICU) | | PedsQL | PedsQL | PedsQL | PedsQL | PedsQL | PedsQL |
|  |  | *****SIHQ** |  |  |  |  |  |
|  |  |  |  |  | PEDI-CAT | PEDI-CAT | PEDI-CAT |
|  |  |  |  |  | WIDEA-FS | WIDEA-FS | WIDEA-FS |

**^§^**Bayley-4 Motor, Cognitive, and Language modules only

*Bayley-4 motor score at 12-months corrected age is primary outcome measure

**GMA will not be scored when infant is 46-48 weeks PMA, but video and sensor data will be acquired

***SIHQ = Social Influencers of Health Questionnaire. Note that not all answers will be recorded as part of this study

**Note**: The number of assessments performed up to 3 months corrected age may vary based on age at enrollment

- **Bayley Scales of Infant and Toddler Development Fourth Edition (Bayley-4):** The Bayley Scales of Infant and Toddler Development Fourth Edition (Bayley-4) is a five-domain assessment tool used to determine developmental delays in children, from the age of 16 days until 42 months. The developmental domains covered in this assessment tool are cognitive, language, motor, social-emotional, and adaptive behavior. The cognitive, language, and motor domains are assessed by administering items to the child, whereas the social-emotional and adaptive behavior domains are assessed via caregiver-completed questionnaires: The assessment is in-person and takes approximately 15-40 min on average, with longer times for older infants. Infants may be video recorded during this assessment. This is a routine test in the Early Childhood Clinic.
- **The General Movements Assessment (GMA):** This assessment is designed to identify neurological issues that may lead to delay (i.e., cerebral palsy or developmental disabilities). Appropriate age range for assessment is from birth until 20 weeks CA. For the assessment, the infant, ideally in a calm alert state, is placed in a supine position and video-recorded from above. Generally, the video recording is for approximately 5 minutes, however, the infant may be recorded for up to 30 minutes to achieve an accurate representation of the infant’s movements. This assessment will be performed twice, once while the infant is wearing sensors and once without sensors. Individuals formally trained in the GMA will score the assessment. This is a routine test at term age in the NICU and at 3 months corrected age in the Early Childhood Clinic.

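### The primary 12-month comparison uses only infants with a 12-month score, and planned attrition of 20–30% is met only by enrolling more, although 6-month Bayley-4 Motor scores could reduce the risk of bias

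*Protocol*

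**What the plan says.** Under *Data analysis*, "The primary analysis to compare 12-month Bayley-4 Motor scores between treatment arms" "will be performed using a two-sample two-sided t-test assuming equal variance", with a Wilcoxon rank-sum test if normality fails. In addition, "a covariate adjusted estimate will be obtained using a linear regression model adjusted for known baseline prognostic factors", with neuromotor risk, gestational age and sex as examples. No earlier score and no imputation is mentioned for the primary outcome.

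Under *Power Analysis* the trial is sized on 77 infants per arm: "Assuming 30% attrition, up to 220 patients (110 per arm) will be required in order to obtain 154 patients evaluable for primary outcome". At 20% attrition the figure is 192.

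Table 1 (under *Procedures Involved*) puts both arms on one timeline, with the Bayley-4 at 6 and 12 months corrected age. Its footnote, "Bayley-4 Motor, Cognitive, and Language modules only", confirms that the Motor module is given each time. AIMS is scheduled at 6, 9 and 12 months.

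For Aims 2 and 3, *Data analysis* plans linear mixed models with repeated measures and remarks that "this approach appropriately deals with missing data by including all evaluable observations across time points, rather than performing a complete case analysis".

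**The concern.** The t-test, the Wilcoxon fallback and the baseline-adjusted regression all need an observed 12-month score. Over-enrolment keeps the number analysed at 154, but it does not make those 154 representative of the infants randomised. If infants doing poorly leave one arm more than the other, the observed difference is shifted, in either direction.

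The protocol gives reasons to take this seriously:
- *Randomization* says that the study is not blinded.
- Intervention families are asked for up to two sessions a week plus at least 20 minutes of activities on 5 days a week; control families are not (*Study Intervention(s)*).
- *Withdrawal of Participants* lets the PI withdraw infants on grounds of medical stability or compliance. The first depends on health, and the second may depend on arm.

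Meanwhile a 6-month score on the same scale is collected in both arms and plays no part in the primary analysis.

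**Working it through.** **1. The plan's own figures.** Inputs from *Power Analysis*: "two-sided α=0.05 significance level to detect an 8-point difference in Bayley-4 motor scores at 12 months", SD 15 (or 17.5), 77 per arm.
- Noncentral t power: 90.8% at SD 15 (stated 90.1%) and 80.5% at SD 17.5 (stated 79.4%). These are close enough.
- Enrolment = 154/(1 − d): 154/0.70 = 220 (stated 220); 154/0.80 = 192.5 (stated 192).
- Planned loss at 30%: 220 − 154 = 66, or 33 per arm.

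**2. Bias, worked by hand.** Assumptions not in the protocol: the lost infants in one arm scored 7.5 points (0.5 SD) lower at 6 months than those retained; the 6-to-12-month correlation is 0.6 with equal SDs; loss in the other arm is unrelated to score.
- Expected 12-month gap, lost against retained: 0.6 × 7.5 = 4.5 points.
- Error in that arm's observed mean: 0.30 × 4.5 = 1.35 points.
- Share of the 8-point target: 1.35/8 = 17%.
- With the same gap and the same loss in both arms, the two errors cancel in the difference.

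**3. What 6-month scores recover.** Assume further that half of those lost in each arm (16.5) have a 6-month score, and that they are typical of all those lost.
- Shift in that arm's 6-month mean once they are included: 7.5 × 16.5/93.5 = 1.32 points.
- Correction carried to 12 months: 0.6 × 1.32 = 0.79 points.
- Bias left: 1.35 − 0.79 = 0.56 points. If all 33 had a 6-month score, none would be left.

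**4. Precision.** Variance of an arm mean relative to 77 completers, with loss confined to a late drop-out (large-sample form): (1 − r²) + r² × 77/93.5.

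| r | ratio | variance saved | equivalent n per arm |
|---|---|---|---|
| 0.5 | 0.956 | 4% | 77/0.956 ≈ 81 |
| 0.6 | 0.936 | 6% | 77/0.936 ≈ 82 |
| 0.7 | 0.914 | 9% | 77/0.914 ≈ 84 |

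**5. Simulation.** 110 per arm, 30% missing at 12 months, SD 15, 4,000 runs per scenario. Assumptions: correlation 0.5 or 0.7; 6-month effect 4 points (0 under the null); log-odds of drop-out changing by 0.7 per SD of the 6-month score where loss is score-related; half or all of those lost have a 6-month score. The alternative is a bivariate-normal likelihood estimate from both visits.

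| Loss pattern | Completer t-test | 6- and 12-month model |
|---|---|---|
| Unrelated to score | unbiased, power 90–92% | unbiased, power 91–95% |
| Low scorers leave control only, true effect 8 | estimate 6.0–6.6, power 69–77% | all 6-month scores: about 8.0, 92–94%; half: 7.2–7.4, 86–88% |
| Low scorers leave intervention only | estimate 9.5–10.1 when the truth is 8; type I error 9–14% under no effect | type I error about 5% (all) or 6% (half) |

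With low scorers leaving both arms in the same way, a separate large-sample run showed negligible bias in the completers' difference.

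**The case against.** Several objections have force.
- A reader might infer that the t-test is valid only if scores are missing completely at random. That is too strong. The arm difference is also unbiased if loss depends on arm alone, and nearly so if it depends on score in the same way in both arms. The protocol contains no evidence that loss will differ; it only makes that plausible.
- A reader might infer that the protocol contradicts itself. It does not. The remark on complete-case analysis concerns models for change over time in the Aims 2 and 3 outcomes, some of them exploratory, while the primary question concerns one time point. What stands is that the primary outcome gets none of the protection that the protocol credits to the other analyses.
- The baseline-adjusted regression tolerates loss that depends on arm and the included baseline factors, if correctly specified. It is supportive only, and it cannot use how the infant has developed since birth.
- The protocol never says that only completers are analysed, and imputation or sensitivity analyses may sit in a statistical analysis plan that is not shown. But the protocol names the primary test, and that test needs a 12-month score.
- Retention is well supported: missed visits are rescheduled, home assessment is possible, each assessment time point pays $100, monthly payments rise from $25 to $100, and the 12-month Bayley-4 is routine clinic care. These measures should lower the loss, yet the protocol still plans for 20–30%.
- A 6-month score does nothing for infants lost earlier, including those dropped on transfer from the NICU to the PICU.

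**Conclusion.** The point holds as a weakness in the chosen primary method. The size of any bias cannot be known in advance. Under the assumptions in the working, loss of low scorers from one arm shifts the estimate by 1.35 points by hand calculation, or about 1.4–2.0 points in simulation, against the target of "a Bayley motor score that is 8 points (~0.5 SD) higher in the intervention group than in the control group". It is near zero if drop-out is alike in the two arms.

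Two stronger readings are not supported. Simulated drop-out in opposite directions in the two arms gives a bias of 3–4 points and a type I error of 22–41%, but nothing in the protocol suggests that pattern. Nor would the alternative analysis remove the bias in general: it does so only if loss is explained by scores actually observed. With half of the 6-month scores available, about 0.56 of the 1.35 points remains. The precision gain is modest, 4–9% of variance.

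**What to change.** Name as the primary estimate one of the following, before any outcome data are analysed, including at the interim:
- the 12-month arm contrast from a likelihood repeated-measures model of Bayley-4 Motor at 6 and 12 months, with arm by time, risk stratum and site, and an unstructured covariance, in all randomised infants with any such score; or
- the baseline-adjusted 12-month regression with multiple imputation done separately by arm, using the 6-month Bayley-4 and the 6- and 9-month AIMS.

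Keep the two-sample t-test on observed 12-month scores as a sensitivity analysis. In *Power Analysis*, state that the t-test calculation is a conservative approximation for the new model (when loss is unrelated to score). State openly that the analysis assumes missing at random given the observed scores, and that it gains little for infants lost before 6 months.

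The cost is a change of wording in *Data analysis* and *Power Analysis*. PROC MIXED is already planned, and no visit or measurement is added.
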